### Process evaluation and discrete choice experiment (DCE)

Optional semi-structured interviews, with people with MCI, dementia, carers, GPs, and practice managers/admin staff who participated in the intervention, will be used to explore the process evaluation of intervention acceptability, feasibility and fidelity [81]. We will also aim to interview GPs/Practice Managers who chose not to participate or who dropped out of the study.

Interested participants will be interviewed once, and interviews will take place either near the start of the intervention, following completion of the intervention, or during follow-up, and last no more than 45 min. GPs, research nurses and administrators will also be presented with a brief, optional online survey, to share their experience on the design and delivery of the intervention and research methodology. Interview topic guides, informed by Normalisation Process Theory (NPT) [82], will be structured according to key elements to understand successful or unsuccessful implementation of a new intervention.

Analysis of process evaluation interviews and questionnaires will illuminate contextual factors that affect whether the intervention is used by PLWD/MCI, carers, and GPs as intended and whether it has had a positive impact. This will also inform assessments on the fidelity of the intervention delivery against a fidelity checklist and the intervention approach (i.e. to check that it is person-centred). The fidelity checklist will include items such as ‘was there a discussion about sleep disturbance’, participant completion of all SADL sub-elements, GP inclusion of 3E’s and goal setting in the tailored health plan, and participant attendance at GP consultations to co-develop and revise the tailored health plan. Any issues that patients or carers have in completing the SADL or attending GP consultations will also be captured in the process evaluation.

An optional DCE survey, following good practice [83–86], will be delivered to patients, carers, and GPs at Baseline and 15-week follow-up, and take up to 20 min to complete at each timepoint. Agreement to participate in the DCE will be obtained during consent (optional consent statement). Collection of DCE data from all participants who consented to participate in the DCE will be coordinated by collaborating researchers at the University of Exeter and monitored by the Trial Management Group. The DCE will be used to better understand preferences of intervention delivery. Outputs of the process evaluation and DCE will refine the programme theory and inform the design for the definitive cRCT. Participation in Process Evaluation and DCE was considered optional, as contribution from a relatively small proportion of the overall target sample size was required for meaningful interpretation of results.

### Health economic outcomes

The intended primary economic outcome measure for the definitive trial is the cost per quality adjusted life years (QALYs) [76], which will be obtained from the EQ-5D-5L, a generic measure of health related quality of life (HRQoL), and is recommended by NICE for use in health technology assessments to estimate the cost-per-QALY of interventions and to inform healthcare policy decisions across the NHS. We will also assess the feasibility of estimating cost-effectiveness for a definitive cRCT by collecting data from the DEMQOL self-rated and DEMQOL proxy, which will provide a dementia-specific measure of patient HRQoL. Health state valuations (HSVs) from carer responses to DEMQOL proxy will be derived using published and validated indices, the “DEMQOL-proxy-U” [74]. We will also assess the feasibility of collecting self- and proxy-reported data from the ICECAP-O (including adults both < 65 and ≥ 65 years), to provide a measure of patient wellbeing that is suitable for use in economic evaluation (ICECAP-O will be used instead of ICEAP-A for adults < 65 to allow comparable analysis in this study, as validity of both instruments has been confirmed in age groups 50–70 [78]. This will involve deriving wellbeing values from proxy carer responses to the ICECAP-O, using a published and validated index, which was developed to enable the cost-effectiveness of health and social care interventions to be assessed in terms of their impact on the wellbeing of older patients or care recipients, beyond the usual remit of HRQoL measures [77].

### Safety reporting

This is a low-risk intervention study (as identified with a risk assessment), which includes an older population who are expected to experience acute illness resulting in hospitalisation, development of new medical conditions and deterioration of existing medical conditions. Safety of the intervention is not an outcome measure, and the individual components of the intervention are not novel in this patient population. To reduce excessive unnecessary data collection, burden on clinical staff, and reduce the amount of sensitive patient data that is collected for research purposes, a risk-proportionate approach to the collection and reporting of safety data was taken. Only Serious Adverse Events (SAE) from patient participants will be recorded and reported. SAEs are considered as any untoward medical occurrence that results in death; is life-threatening; requires inpatient hospitalisation or prolongation of existing hospitalisation; results in persistent or significant disability/incapacity. SAEs will be recorded from the point of participant consent, or consultee declaration, to the final follow-up assessment at 15 weeks when participation in the study ends. All SAEs will be reported to Exeter CTU within 24 h of the participating site becoming aware of the event (not from the time of the event occurring). This should be done by site staff on the EDC System (REDCap). Causality of reportable SAEs will be assessed by the site PI (or authorised delegate). All SAEs which are possibly, probably or definitely related to the intervention will be categorised as ‘related’. All related serious adverse events are considered unexpected and will be categorised as RUSAEs and subject to expedited reporting to the Sponsor, DMC, PSC and lead REC. Causality of all SAEs will be assessed by the site PI (or authorised delegate).

### Patient and public involvement (PPI)

Diverse PPI groups with lived experience, coordinated by Innovations in Dementia (iD), Together in Dementia Everyday (TiDE), Chinese Wellbeing, alongside co-applicant and PPI co-lead [name] (PLWD) and a South Asian PPI group, were involved in identifying the area of research and advising on study design from the funding application stage, through to the development and revision of all study documents and trial procedures. The TIMES intervention was developed through a series of co-designed workshops, with input from PLWD and MCI, family and professional carers with lived experience, GPs, healthcare professionals, social prescribers, and secondary care sleep clinicians [87]. Two independent PPI representatives sit on the Programme Steering Committee (PSC).

## Analysis plan

### Sample size calculation

As this is a feasibility study, the aim of the trial is not to determine the effectiveness of the intervention, but rather to estimate key feasibility parameters to inform the design of a subsequent definitive randomised trial. Consequently, no formal power calculation has been undertaken to determine the required sample size. For a total of 64 patient participants, the 95% confidence interval for follow-up will be estimated to within ± 10 percentage points, assuming a follow-up rate of 80%. This sample size will therefore be sufficient to estimate the standard deviation of outcome variables at baseline and at follow-up for each treatment group, assuming 25 participants (patient and caregiver) provide follow-up data, and assuming a medium or small effect size [88].

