## Data collection

### Randomisation and blinding

#### Randomisation is at the GP practice (site) level

Ten GP practices will be randomised in batches of two sites at once, with the static list’s site number generated by the unblinded Trial Statistician (or delegate). A Trial Manager who is blinded to the static randomisation list will request the Trial Statistician to allocate treatment arms based on the order of site confirmation of capacity and capability. Requests for site confirmation of capacity and capability will be completed simultaneously in blocks of two. Five practices will be allocated to each study arm (1:1 allocation ratio), using a block design (i.e. five blocks of two practices each). Randomisation will not be stratified.

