## Progression criteria

Criteria for determining whether to proceed to a definitive trial have been reviewed and agreed by an independent Programme Steering Committee (PSC) (Table 4). Any ambiguity in meeting the overall progression criteria will be made by the PSC in conjunction with the Funder.

**Table 4 Tab4:** Summary of progression criteria to definitive trial

	Definite Stop, i.e. abort definitive cRCT	Review required, i.e. PSC to determine progression to definitive cRCT	Definite Go i.e. proceed to definitive cRCT
Feasibility: recruitment rate	< 25% of invited eligible people consenting to participate	25–79% of eligible people consenting to participate	≥ 80% of eligible people consenting to participate
% of target sample size recruited	< 50%	50–99%	100%
Acceptability: retention to trial	< 25% of participants complete all three stages of the intervention	25–89% of intervention participants complete all three stages of the intervention	≥ 90% of intervention participants complete all three stages of the intervention
Completeness of outcome data	< 25% of participants complete key outcome data at 15-week follow-up	25–89% of participants complete key outcome data at 15-week follow-up	≥ 90% of participants complete key outcome data at 15-week follow-up
Process evaluation	Evidence that the intervention cannot be delivered with fidelity and that it is not acceptable to participants and professionals	Inconclusive evidence that the intervention can be delivered with fidelity and that it is acceptable to participants and professionals	Evidence that the intervention can be delivered with fidelity and that it is acceptable to participants and professionals

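### The stated precision for follow-up (within 10 points at 80%) is the figure for 64 independent patients; with patients recruited in 10 practices it holds only if the practice ICC for follow-up is at most about 0.008

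*Protocol article*

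**What the plan says.** Under Sample size calculation, the protocol article says that "no formal power calculation has been undertaken to determine the required sample size" and gives a precision instead. "For a total of 64 patient participants", it says, "the 95% confidence interval for follow-up will be estimated to within" plus or minus "10 percentage points, assuming a follow-up rate of 80"%. A further sentence says the sample will suffice to estimate outcome standard deviations, but attaches no width. The follow-up figure is therefore the only numerical precision in the section. The section mentions no ICC, design effect or grouping by practice.

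Elsewhere the article treats practice as a source of correlation:

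- **Screening and recruitment:** 64 dyads are to be recruited from 10 practices.
- **Randomisation and blinding:** practices are the unit of allocation. "Five practices will be allocated to each study arm (1:1 allocation ratio").
- **Statistical analysis:** the mixed models for continuous outcomes carry a random practice effect and a small-sample correction.
- **Table 3, Objective B:** an ICC is to be estimated for the proposed primary outcome.

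The co-primary objectives define acceptability as the percentage of intervention participants who complete all three stages. Table 4 judges that percentage, and the percentage "of participants complete key outcome data at 15-week follow-up", against a Go line of 90%.

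**The concern.** Patients in the same practice may be alike in whether they are followed up. If they are, 64 patients in 10 practices carry less information than 64 independent patients, and the interval is wider than stated. The protocol accepts this reasoning for the continuous outcomes but not for the one precision it quotes.

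The steering committee will read the feasibility percentages against the bands of Table 4. It should know how uncertain they are. That applies most to acceptability, which is measured in one arm only and has no stated precision.

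**Working it through.** **Inputs from the article.** n = 64 patients; follow-up p = 0.80; 95% confidence; 10 practices, five per arm; 32 patients per arm. Mean practice size is 64/10 = 6.4 overall and 32/5 = 6.4 in the intervention arm.

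**Assumed.** The article gives no ICC for follow-up or for completion of the intervention, so I use 0.01, 0.05 and 0.10. I take practices as equal in size; unequal sizes would widen the intervals.

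**Step 1: reproduce the stated figure.** With independent patients, SE = sqrt(0.8 x 0.2/64) = 0.050, and the half-width is 1.96 x 0.050 = 9.8 points. The stated 10 points reproduces, with 0.2 points to spare.

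**Step 2: the ICC at which the statement stops holding.** The design effect is DE = 1 + (6.4 - 1) x ICC = 1 + 5.4 x ICC. The largest DE that keeps the half-width at 10 points is (10/9.8)^2 = 1.041, so ICC = 0.041/5.4 = about 0.008.

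**Step 3: half-width at 80% follow-up, over the assumed range.** Half-width = multiplier x 0.050 x sqrt(DE), with multiplier 1.96 (z) or 2.262 (t, 9 df for 10 practices).

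| ICC | DE | Effective n (64/DE) | z, points | t (9 df), points |
|---|---|---|---|---|
| 0 | 1.000 | 64.0 | 9.8 | 11.3 |
| 0.01 | 1.054 | 60.7 | 10.1 | 11.6 |
| 0.05 | 1.270 | 50.4 | 11.0 | 12.7 |
| 0.10 | 1.540 | 41.6 | 12.2 | 14.0 |

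The t column illustrates one small-sample method. The article names no interval method for proportions, so the comparison with the stated figure uses the z column.

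**Step 4: acceptability, intervention arm only.** At 90% with 32 independent patients, 1.96 x sqrt(0.9 x 0.1/32) = 10.4 points. That upper limit is 90 + 10.4 = 100.4%, so a symmetric interval is unsuitable here. The Wilson interval stays below 100%. Its centre is (p + z^2/2n)/(1 + z^2/n), and its half-width is z/(1 + z^2/n) x sqrt(p(1 - p)/n + z^2/4n^2). With p = 0.90 and n replaced by 32/DE:

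| ICC | Effective n | Wilson 95% interval | Half-width, points |
|---|---|---|---|
| 0 | 32.0 | 75.0% to 96.4% | 10.7 |
| 0.05 | 25.2 | 72.6% to 96.8% | 12.1 |
| 0.10 | 20.8 | 70.4% to 97.2% | 13.4 |

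These intervals make no small-sample correction for having only five practices; one would widen them.

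**The case against.** **The shortfall depends on an unknown ICC.** This stands. A reader might infer that the design cannot deliver 10 points. The article does not support that: at an ICC of 0.008 or less the statement is true (z), and at 0.01 it misses by 0.1 point. Nor does the article show that follow-up clusters strongly. Blinded research nurses collect outcomes by phone or in person, and site staff are mentioned only for chasing missing data fields. The article does not say that nurses are assigned by practice.

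**At higher follow-up the figure survives.** Also true. At 90%, the independent half-width is 1.96 x sqrt(0.9 x 0.1/64) = 7.3 points, and it stays within 10 until the ICC reaches about 0.16, from ((10/7.35)^2 - 1)/5.4. But the protocol makes its claim at 80%.

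**The 80% planning rate lies below the 90% Go line.** A reader might infer an error. There is none. For precision 80% is the cautious choice, because it gives a wider interval than 90%. Table 4 makes 25 to 89% a permitted Review outcome. If true follow-up is 80%, the chance of at least 58/64 is 1.8% with independent patients; a rule that seldom returns Go for a rate below its line is working as intended.

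**Is follow-up a primary measure?** A reader might infer that the precision concerns a quantity outside the primary objective. The co-primary objectives name only consent and completion of the three stages, but Table 3 lists retention with valid outcome data under Objective A. The inference fails.

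**Little hangs on it.** Table 4 uses observed percentages, and ambiguity goes to the steering committee and funder. A half-width 1 to 2 points larger changes no listed rule. This limits the weight of the point but does not make the sentence right.

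**Interval methods belong in the SAP.** This is fair as to the choice of method. The precision claim, however, is made in the protocol.

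**Conclusion.** The point holds in a limited form. The plan's arithmetic is correct for 64 independent patients, but that assumption does not match recruitment in 10 practices or the protocol's own analysis model. The 10-point statement is met by a normal-based interval only for a follow-up ICC up to about 0.008. For an assumed ICC of 0.05 to 0.10 the half-width is 11.0 to 12.2 points by z, or 12.7 to 14.0 by t with 9 df.

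Acceptability is less precise: about 10 points at 90% before clustering, and more with it. The section does not say so.

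The conclusion rests on an assumed ICC range and equal practice sizes. It is a modest overstatement of precision; it does not show that 64 dyads are too few for a feasibility trial.

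**What to change.** 1. In Sample size calculation, do one of two things. Either restate the half-width at 80% follow-up as about 11 to 12 points for an assumed practice ICC of 0.05 to 0.10, naming the ICC and the normal-based method; or keep 10 points and say that it assumes negligible clustering by practice. If a t-based figure is preferred, give it separately as 12.7 to 14.0 points with 9 df, so that z and t results are not merged into one range.
2. Add that acceptability rests on about 32 patients in five practices and is less precise: about 10 points at 90% if patients were independent, wider with clustering. Use an interval that cannot pass 100%.
3. State that confidence intervals for the feasibility proportions will allow for clustering by practice, with the method given in the SAP.

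The cost is wording in the protocol and SAP and a slightly less favourable stated figure. No extra patients are needed, and neither the 80% planning rate nor the Table 4 thresholds need to change on this account.

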### Statistical analysis

A detailed Statistical Analysis Plan (SAP) will be produced by the trial statisticians (FW, PG) and the lead/senior statistician (LS), in collaboration with the Programme Management Group (PMG). The SAP will be reviewed by the Data Monitoring Committee (DMC) and by the PSC, then finalised and signed off by the trial statisticians and CI, and the independent statistician on the PSC, before completion of data collection. The SAP and Protocol will be made available upon request to the Sponsor.

Participant and carer baseline demographic and outcome data will be summarised. Specifically, continuous data will be reported as means and standard deviations, or as medians and interquartile ranges if the data appear skewed. Categorical data will be reported using numbers and percentages. A CONSORT flow diagram will be produced to illustrate the flow of participants through the trial. Specifically, the number of participants approached, eligible, consented and recruited, and assessed at baseline, and at 9- and 15-week follow-up, will be illustrated, along with the number of participants withdrawn or lost to follow-up between each data collection time point. The reasons for ineligibility, eligible participants not being recruited, and for withdrawal post-consent, will also be presented where available. To participate in the trial, both the patient and their carer need to be eligible and willing to consent. As a result, we will also present the ineligibility and unwillingness to participate figures, broken down by patient and carer.

An objective of this feasibility study is to assess the completeness of the primary and secondary outcomes proposed for the definitive trial. Summary statistics, including mean differences and CIs, for each continuous outcome at baseline and at 9- and 15-week follow-up will be presented by treatment group. In addition, mixed linear regression models will be performed to produce a between-group mean difference and associated 95% confidence interval at 15-week follow-up for continuous outcomes. Linear mixed regression models will be performed with adjustment for baseline values and centre, i.e. region, and will include a random effect on cluster (practice), with a small sample correction to accommodate for the small number of clusters sampled. For SDI (the putative primary outcome for the definitive trial), we will derive a binary variable at all time-points to indicate whether or not the patient participant had at least one (of seven) symptoms with scores (frequency × severity) of ≥ 4 [67]; this binary variable will be reported descriptively by treatment group. All analyses will follow the treatment policy approach, i.e. participants will be analysed according to their randomised group irrespective of treatment actually received. All analyses will use observed data only. If individual items within a patient-reported outcome measure (questionnaire) are missing, these may be imputed in line with instrument-specific published guidance or scoring instructions, or other method as agreed by the trial team. However, no between-person imputation (e.g. multiple imputation for dropouts) is planned.

As this is a feasibility study, no inferential subgroup analyses will be undertaken. However, it is of interest to explore the feasibility outcomes separately for participants with dementia and for those with MCI, as well as participants with family and professional carers. As a result, the summary descriptive statistics for each putative outcome measure will be presented within treatment group for participants with PLWD and participants with MCI separately, and for participants with family carers and those with professional carers separately. All analyses of continuous outcome measures will be adjusted for baseline values. There will be no sensitivity analyses with further adjustment for participant characteristics, even if unbalanced by treatment group, due to the feasibility nature of the trial. There are no planned interim analyses or criteria for early termination of the trial. No sensitivity analyses using imputed data for those participants who do not have observed outcome data will be performed. Further detail will be provided in the SAP. The degree of missing data for each outcome at each time point will be reported to inform the design of a subsequent definitive trial.

Qualitative interviews and surveys for process evaluation will be analysed using open coding techniques, leading to thematic descriptions of the combined datasets. The analysis will reflect the core constructs of Normalisation Process Theory (NPT), adding the patient/carer’s perspective, which will enable findings, coherently embedded in the NPT framework, to inform future implementation.

### Health economic analysis

We will describe mean costs and mean effects, presenting disaggregated costs and consequences. Methods will be designed for capturing: (i) the resources required to deliver the intervention; (ii) health, social and wider care service resource use; (iii) health economic outcomes relating to HRQoL and capability wellbeing. These findings will inform the development of future economic evaluation to be undertaken alongside the definitive cRCT to: (i) establish the resources required to provide the intervention, (ii) estimate intervention costs, and (iii) conduct a full cost-economic analysis (CEA). The intervention costing and CEA, based on within-trial data collection, will be undertaken against a primary perspective of the NHS/Social Care, with participants and broader societal perspectives considered in sensitivity analyses. The future CEA will synthesise cost and outcome data to present an incremental cost-effectiveness ratio (ICER) for the primary economic endpoint of policy relevance, including cost per quality-adjusted life-year (QALY).

Descriptive statistics will be presented for dementia-specific HSVs and wellbeing values at each assessment point (mean, standard deviation, range) and for QALYs and WALYs over the 15-week follow-up period, calculated using the standard AUC approach. We will use an intention-to-treat analysis, taking the previously mentioned NHS and social care perspective. No subgroup analysis will be conducted as this is a feasibility trial and not powered for inferential analyses. As this is a feasibility trial, we will report descriptive data only for each trial arm, with confidence intervals for between-group comparisons. No *p*-values will be reported. Primary analysis will be based on complete case data, in which each individual analysis will be based on observed (i.e. not imputed) data from participants with completed fields that are required for each respective analysis. Losses to follow-up at data collection points will be presented for both primary and secondary outcomes. Missing outcome data will also be discussed, along with its causes. Outputs from the feasibility study will follow CHEERS reporting conventions [89].

